**Fig. 3 Fig3:**
[figure not shown]
Flow chart of work-up RACER study. *Left arm*: standard care group; *right arm*: CESM group

### Sample size calculation

Prior research showed a specificity of FFDM of 40% in this population [5]. To enable detection of a clinically relevant increase of specificity by 15% (from 40% to 55%), 176 patients without malignant disease per group are required (power 80%, alpha = 5%). The prevalence of malignant lesions in women recalled from the breast screening program is about 30%; thus, 70% have benign lesions. Therefore, a total of 251 women per group (176/0.7) has to be included. To account for 5% loss to follow-up, the final number of patients to be included is 528 (502/0.95). The calculations were done with OpenEpi [20].

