## Abstract

**Background:**

In the Dutch breast cancer screening program, women recalled with a BI-RADS 0 score are referred for additional imaging, while those with BI-RADS 4/5 scores are also directed to an outpatient breast clinic. Approximately six out of ten women are recalled without being diagnosed with a malignancy. However, these recalls require additional imaging and doctor visits, which result in patient anxiety and increased health care costs. Conventional types of imaging used for additional imaging are full-field digital mammography and tomosynthesis. Contrast-enhanced spectral mammography has proved to have higher sensitivity and specificity than conventional imaging in women recalled from screening. Therefore, the aim is to study if CESM instead of conventional imaging is a more accurate, patient-friendly, and cost-effective strategy in the work-up of women recalled from breast cancer screening.

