## Background

In the Netherlands, a national breast cancer screening program was introduced in 1990, with full implementation being completed in 1997. All women aged 50–75 years receive an invitation to participate biennially. At mobile screening units, full-field digital mammography (FFDM) is performed. By default, two images are made per breast, one in cranio-caudal (CC) view and one in mediolateral oblique (MLO) view. The images are independently screened for suspicious lesions by two certified screening radiologists. In the case of discrepancy, a third (senior and unblinded) radiologist will make the final decision regarding referral. In the screening recalls, a distinction is made between Breast Imaging Reporting and Data System (BI-RADS) 0 score and BI-RADS 4 or 5 score recalls [1]. Women recalled with a BI-RADS 0 score are directly referred by their general physician (GP) for additional imaging. Women recalled with a BI-RADS 4 or 5 score are first referred by their GP to an outpatient breast clinic, before being directed to a radiology department for additional imaging [2].

Conventional additional imaging may consist of additional (special) FFDM images or digital breast tomosynthesis (DBT), which can be combined with other imaging modalities, such as breast ultrasound (US). Based on the findings during the imaging work-up, tissue sampling might be recommended: either core needle biopsy (CNB), vacuum-assisted biopsy (VAB), or fine-needle aspiration cytology (FNAC). The total work-up in the evaluation of the recalled women can also be extended with breast magnetic resonance imaging (MRI) (e.g., in inconclusive findings) or 6 and/or 12 months follow-up with FFDM, DBT, and/or US.

Approximately six out of ten recalled women from the Dutch breast screening program are not diagnosed with breast cancer [3]. These recalls generate patient distress and anxiety as well as additional doctor visits, medical imaging, and health care costs [3–5]. Also, participation rates for subsequent screening rounds decrease after a recall of women without malignancy [6].

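### The cancer-free share behind the sample size (70%) conflicts with the share given in the Abstract and Background (about 60%), so 80% power is not assured

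*Protocol article*

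**What the plan says.** The Sample size calculation section builds the total in four steps.

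- Control specificity: "Prior research showed a specificity of FFDM of 40% in this population".
- Target and requirement: a "clinically relevant increase of specificity by 15% (from 40% to 55"%), for which "176 patients without malignant disease per group are required (power 80%, alpha = 5"%).
- Conversion from cancer-free women to recalled women: "The prevalence of malignant lesions in women recalled from the breast screening program is about 30%; thus, 70% have benign lesions", so that "a total of 251 women per group (176/0.7) has to be included". No source is cited for the 30%.
- Loss to follow-up: "To account for 5% loss to follow-up, the final number of patients to be included is 528 (502/0.95").

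Two other places give a different cancer-free share. The Background section, citing reference 3, says: "Approximately six out of ten recalled women from the Dutch breast screening program are not diagnosed with breast cancer". The Background paragraph of the Abstract says: "Approximately six out of ten women are recalled without being diagnosed with a malignancy".

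The Study population section makes all women recalled from the national programme eligible, apart from those with contrast allergy, renal insufficiency or nephropathy risk. The Statistical analysis section names a chi-square test for differences in proportions between the arms.

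**The concern.** Six in ten without cancer implies about 40% with cancer, against the 30% used to size the trial. Both statements describe women recalled from the same programme, without restriction to a subgroup. The eligibility rules give no reason why enrolled women should differ from recalled women by ten points.

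The share matters because specificity is the only parameter for which a sample size is given, and its denominator is the cancer-free women. The share therefore scales the total directly. A lower share means fewer women in the powered comparison for the same 528 recruits. At stake is whether the stated 80% power can be relied on for the 15-point difference that the protocol itself calls clinically relevant.

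**Working it through.** **Inputs.** From the Sample size calculation: specificities p1 = 0.40 and p2 = 0.55, power 80%, alpha 5%, 528 women, 5% loss, cancer-free share 0.70. From the Abstract and Background: cancer-free share about 0.60. Assumptions: a two-sided test (sidedness is not stated, but two-sided is what comes close to the printed 176), equal arms (implied by the per-group figures), and the chi-square test without continuity correction.

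**Step 1: reproduce the plan's figure.** With mean proportion p̄ = (0.40 + 0.55)/2 = 0.475,

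n = [1.960 × √(2 × 0.475 × 0.525) + 0.842 × √(0.40 × 0.60 + 0.55 × 0.45)]² / 0.15²

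= [1.960 × 0.7062 + 0.842 × 0.6982]² / 0.0225 = 172.8, so 173 per group.

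The printed 176 is within 2% of this and slightly on the safe side. With a continuity correction the requirement would be 186, and with a one-sided test 136, so neither variant fits as well. The onward steps also reproduce: 176/0.7 = 251.4 and 502/0.95 = 528.4.

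**Step 2: evaluable women per arm.** 528 × 0.95 / 2 = 250.8.

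**Step 3: power by cancer-free share.** The number of cancer-free women per arm is n = 250.8 × share, and

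power = Φ[(0.15 − 1.960 × 0.7062/√n) / (0.6982/√n)].

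The last column is the difference above 40% at which the same formula gives 80% power.

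| Cancer-free share | Cancer-free women per arm | Power, 40% vs 55% | Difference detectable with 80% power |
|---|---|---|---|
| 70% | 175.6 | 80.6% | 14.9 points |
| 65% | 163.0 | 77.7% | 15.4 points |
| 60% | 150.5 | 74.3% | 16.1 points |

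For the 60% row: √150.5 = 12.27; 1.960 × 0.7062/12.27 = 0.1128; 0.6982/12.27 = 0.0569; (0.15 − 0.1128)/0.0569 = 0.653; Φ(0.653) = 0.743.

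**Step 4: checks.**

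- Exact enumeration of the uncorrected chi-square test gives 75.9% at 150 per arm and 74.4% at 151, in line with the approximation.
- With no loss to follow-up, a 60% share gives 264 × 0.6 = 158.4 per arm and 76.5% power, still under 80%.
- With a continuity correction, power is lower throughout: 77.5% at a 70% share and 70.4% at 60%.
- Break-even: 173 cancer-free women out of 250.8 is 69%. Any share below about 69% takes power under 80%, so the plan has almost no slack.

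**Step 5: scale of the gap, for information.** Holding 176 per arm at a 60% share would take 176/0.6 = 293.3, so 294 per arm, and 588/0.95 = 619 women in place of 528.

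**The case against.** A reader might infer that 528 women give 74% power and that the 80% claim is simply wrong. The documents do not support that. Both shares are rounded, one as approximately six in ten and the other as about 30% malignant. The 60% figure carries a citation and the 70% figure none, but the cited study is not at hand, so nothing shows which better describes the women who will enrol. A true share near 65% would be close to both statements, and the shortfall is then only about 2 points. This objection stands, and it is why the result has to be given as a range. It does not restore the stated power, because even the 65% midpoint falls short of 80%.

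The second objection is that 15 points is a minimum of interest and the expected gain may be larger. The Discussion reports specificity rising from 42.0% to 87.7% in an earlier retrospective study of recalled women. With 150 cancer-free women per arm, power is already 94% for 40% versus 60%. This limits the practical consequence. It does not answer the point, because the protocol claims 80% power for 40% versus 55%, and the Discussion itself notes that the earlier work was retrospective.

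Third, a reader might suspect that the more convenient figure was chosen. That goes too far. A 70% share helps specificity only. At 60% there would be about 100 cancers per arm (250.8 × 0.4) where 70% gives about 75 (250.8 × 0.3), which improves precision for sensitivity, also listed in the primary outcome.

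**Conclusion.** The point holds as an internal inconsistency of moderate severity. The Sample size calculation uses a cancer-free share of about 70%; the Abstract and Background give about 60% for the same recalled population; and no text reconciles them. Over that range, 528 women with 5% loss give about 74% to 81% power for specificity of 40% versus 55%, and the difference detectable with 80% power is about 15 to 16 points. The stated 80% is therefore not assured on the protocol's own figures.

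This rests on a two-sided 5% test, equal arms, an uncorrected chi-square and the planned 5% loss. It does not show that 70% is wrong or that the calculation was miscomputed: given its inputs, the section reproduces. Nor does a shortfall of at most about 6 points bias the comparison or invalidate the design.

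**What to change.** In the Sample size calculation, state which cancer-free share applies to the women being enrolled and cite its source. Then bring the Abstract and Background into line with it, or explain why they differ. Restate the power along these lines: *with 528 women, 5% loss and 60–70% of recalled women free of cancer, power to detect specificity of 40% versus 55% is about 74–81%, and the difference detectable with 80% power is about 15–16 points.*

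The cost is a sentence or two and a slightly less favourable power statement. Recruitment, endpoint, test and analysis stay as they are.

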### Statistical analysis

The primary objective of the study is to demonstrate that the use of CESM as a work-up tool for women recalled from breast cancer screening is more accurate compared to standard care consisting of conventional imaging. The secondary objectives are to evaluate whether this novel approach is a more patient-friendly and cost-effective strategy in the work-up of women recalled from breast cancer screening, requiring fewer days until final diagnosis and less additional imaging.

Radiologists will prospectively provide a single BI-RADS classification for each exam, where a BI-RADS score of 1–3 will be considered ”benign” and 4-5 ”malignant”. Based on this cutoff, the final BI-RADS score and recall BI-RADS score, the diagnostic performance parameters sensitivity, specificity, PPV, NPV, and AUC under the ROC curve will be assessed as the primary endpoint for both study arms. Differences in proportions between the two randomized groups will be tested for significance with a chi-square test, and the difference in AUCs will be tested using the method proposed by Hanley et al. [21].

Secondary outcomes are QoL, patient anxiety, and cost-effectiveness. The course of scores on QoL with QALY and patient anxiety (STAI) from baseline over time at the six time points will be visualized and differences between groups will be tested using mixed linear models, which account for correlations between repeated measurements. Single and multiple imputation will be used to replace missing data.

Both intention-to-treat and per protocol analyses will be performed. The per protocol population for the primary outcomes are those who got imaging exams based on their group allocation. Women who underwent CESM in the standard care group are excluded from the per protocol analysis. For the secondary outcomes this population can be further specified to those with questionnaires completed at six time points. *P* values < 0.05 will be considered to indicate statistical significance. Analyses will be performed with SPSS (version 25, IBM Corporation, Armonk, NY, USA) and STATA (version 15, StataCorp LLC, College Station, TX, USA).

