Prior retrospective studies have shown that for these women contrast-enhanced spectral mammography (CESM) proved to be an adequate problem-solving tool, reducing the number of false positives while maintaining high sensitivity [3, 5]. Hypothetically, the use of CESM as an imaging work-up in women recalled from screening reduces the number of additional imaging exams and follow-up doctor visits, potentially saving health care costs [7]. Especially for women with dense breasts, CESM seems to be of additional value, since these women are more at risk of undergoing additional imaging or follow-up after recall due to the low sensitivity of FFDM [8, 9]. Moreover, Houben et al. showed that occult breast cancers are detected when using CESM in up to 4% of women in this population, increasing overall accuracy [10].

Therefore, we propose a prospective, multicenter, randomized controlled trial, aiming to study whether a work-up using CESM instead of conventional imaging modalities such as FFDM or DBT (which is the current standard of care) for women recalled from screening is a more accurate, more patient-friendly, and more cost-effective strategy.

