### Primary and secondary outcomes

The primary outcome will be the accuracy assessed by diagnostic performance parameters, such as sensitivity, specificity, positive predictive value (PPV), negative predictive value (NPV), receiver operating characteristics (ROC) curve, and area under the curve (AUC). Radiologists will prospectively provide a single BI-RADS classification for each exam, where a BI-RADS score of 1–3 will be considered ”benign” and 4-5 ”malignant”. The final BI-RADS score (BI-RADS 1–5), based on imaging, will be compared with the BI-RADS score given by the screening program. The accuracy assessed by diagnostic performance parameters will be assessed after the next screening round after approximately 2 years.

Secondary outcomes will be quality of life (QoL), days until final diagnosis, cost-effectiveness, and experienced patient anxiety during a follow-up of 18 months. Three validated questionnaires will be presented at six different time points (at study inclusion; after 2 and 4 weeks; and after 6, 12, and 18 months). QoL will be assessed by the Dutch version of the EuroQol five-dimension, five-level (EQ-5D-5 L) questionnaire, including a visual analog scale (EQ-VAS). This questionnaire is a preference-based instrument used to value health states [11]. The Dutch tariff for the EQ-5D-5L questionnaire, as established by Versteegh et al., will be used to calculate utility scores per health state [12]. Then the quality-adjusted life years (QALYs) will be modeled based on these utility scores. Resource use related to diagnostics will be collected during the trial.

Health-related anxiety, both state and trait anxiety, will be measured by the Dutch version of the State Trait Anxiety Inventory (STAI-DY-1 and STAI-DY-2) questionnaires. Each STAI has 20 items and will be rated on a 4-point Likert scale, scoring 20–80 points per STAI. A higher score corresponds to a higher anxiety level [13].

For the QoL and STAI scores, inter- and intra-patient differences over time from baseline will be compared including those between the intervention and control group. The scores will also be compared between the women with a follow-up exam after 6 or 12 months and those without this follow-up. Figure 1 shows the outcomes defined by the five outcome elements described by Saldanha et al. [14].

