### Informed consent and randomization protocol

All recalled women announced at one of the participating centers will be contacted for study participation. Written informed consent will be obtained and the first EQ-5D-5 L and STAI questionnaires regarding anxiety and current health state will be completed before any other study procedure is carried out. Participants are also asked for their consent to use their data in possible future studies. See Additional file 1 for the informed consent form in Dutch.

Women will be randomized to undergo standard of care (control arm) or CESM (intervention arm). Minimization with stratification factors will be applied in the computer-generated randomization screening and enrollment application software ALEA (version 3.0.2083.212r; ALEA Clinical, Abcoude, the Netherlands). Randomization will be stratified by the following: predominant reason for recall (mass, calcifications, asymmetry, architectural distortion), recall BI-RADS score (BI-RADS 0 versus BI-RADS 4/5), and study center. Enrollment in the four centers, including the master randomization file, will be overseen by the Study Coordinator. During the inclusion visit, written consent will be conducted and data entry will be done by one of the research team members in each center to execute randomization using ALEA. Should a problem occur in including a patient or randomization, the Study Coordinator must be reached so that he can provide assistance. After allocation, patient and radiologist will be informed about the outcome; hence, they are not blinded. However, the radiologist is blinded for the outcomes between the two groups, since the final diagnosis and pathology are not yet known. The outcome assessors and data analysts are blinded for the judgment of the next screening round by the screening radiologists, since accuracy also depends on the next screening round outcome. Each participant is assigned a trial identification number for anonymization, to analyze the data, and further to be used in publications. In each participant’s hospital patient file a statement will be noted about study participation and the assigned intervention or control group. On request, study participation can be ended during the follow-up phase.

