### Establishment of final diagnosis (the reference standard)

For the control group, final diagnoses of the (recalled) breast lesions can be divided into four categories [3, 5]: (1) simple cysts; (2) superposition densities; (3) solid, benign masses; (4) (invasive) breast cancer or ductal carcinoma in situ (DCIS). The first three groups are defined as benign findings. To ascertain a final diagnosis of (1), targeted US is performed, followed by cyst aspiration and a second FFDM of that breast to confirm that the lesion has disappeared. Final diagnosis of (2) requires a minimum of one special view or DBT, including targeted US. To rule out false negative (FN) findings, 6 and/or 12 months follow-up or breast MRI can be considered. Final diagnosis for categories (3) and (4) is acquired with US-guided or stereotactic tissue sampling. If cancer or DCIS is diagnosed, the subject will have a ”true positive” (TP) finding. In subjects where no breast cancer or DCIS is diagnosed, the follow-up period of 2 years will determine the true disease status. If no interval cancers have been detected and the subject has not been recalled in the subsequent screening round, the case will be considered a ”true negative” (TN).

In the CESM group, diagnoses are acquired slightly differently. For (1), CESM will show an ”eclipse sign” which is pathognomonic for cysts [3]. No further action is needed. For category (2), a negative CESM exam with no suspect lesion on both low-energy and recombined images rules out (pre)malignant lesions due to CESM’s high negative predictive value [3, 5]. To acquire final diagnoses of (3) and (4), CESM and targeted US are performed including tissue sampling for pathological confirmation.

Since most benign recalls are caused by cysts or superposition densities, the investigated intervention will most likely result in fewer additional exams and tissue samplings among these recalls [3, 5]. Moreover, follow-up exams can be omitted, which is more patient-friendly, and hypothetically, more women will attend the subsequent screening round when they are examined with CESM.

A flow chart is presented in Fig. 3, summarizing the study design, the randomization process, and the establishment of the different diagnoses.

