Using CESM as a work-up tool also has some limitations. The most important disadvantages are the increased radiation dose and the administration of iodine-based contrast agents. Regarding the increase in radiation dose, several studies have shown that the mean radiation dose of CESM per exposure is in the range of 2.5-2.8 mGy [18, 31–33]. In comparison, the radiation dose of FFDM in these studies varied from 1.4 to 1.8 mGy. Jeukens et al. showed that the CESM radiation dose is approximately 80% higher than that in FFDM: 2.8 mGy versus 1.6 mGy, respectively [18]. Nevertheless, it is still within internationally accepted limits and does not substantially increase breast cancer incidence or mortality in women recalled from screening, who are at least 50 years. We believe that this increased dose is justified in the dedicated population as outlined. The chance of acquiring breast cancer due to this radiation exposure is expressed in the life attributable risk (LAR) numbers. For example, for a single view CESM acquisition having a mean radiation dose of 2.8 mGy per exposure, the LAR number for cancer incidence is 0.4 in 100,000 persons at the age of 60 years [34]. The LAR number for cancer mortality at this age is even 2–3 times lower. Some even advocate that there is no effect of radiation under a dose of 100 mSv. Hence, one may conclude that CESM exposure poses only a small additional risk compared to the lifetime risk for breast cancer incidence and mortality of 12,000 and 3000 cases per 100,000 women, respectively.

Regarding the use of iodine-based contrast, Houben et al. had in clinical practice in a similar population a low incidence (0.6%) of adverse hypersensitivity reactions [10]. In contrast, they also showed that occult cancers are being detected in 3–4% of the recalled women by using CESM. Consequently, the chance of finding occult (small) breast cancers is higher than the chance of having adverse reactions to contrast administrations (which are all documented in the RACER study), which in our opinion would justify the use of a CESM-based work-up of women recalled from screening.

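### Occult cancers that stay silent for two years inflate control-arm sensitivity and NPV, so a real detection gain for CESM can be hidden; report detection per randomised woman alongside

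*Protocol article*

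**What the plan says.** The Protocol article, Statistical analysis, states that "the diagnostic performance parameters sensitivity, specificity, PPV, NPV, and AUC under the ROC curve will be assessed as the primary endpoint". On the comparison it says: "Differences in proportions between the two randomized groups will be tested for significance with a chi-square test". The sample size rests on specificity alone (40% versus 55%).

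The section on the reference standard makes a cancer or DCIS found at work-up a true positive. For the others, "In subjects where no breast cancer or DCIS is diagnosed, the follow-up period of 2 years will determine the true disease status". The condition for a true negative is: "If no interval cancers have been detected and the subject has not been recalled in the subsequent screening round". Accuracy "will be assessed after the next screening round after approximately 2 years", and the randomisation section gives a reason for blinding the assessors to that round: "since accuracy also depends on the next screening round outcome".

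On what CESM is expected to find, the Background reports that "occult breast cancers are detected when using CESM in up to 4% of women in this population, increasing overall accuracy", and the Discussion that "occult cancers are being detected in 3–4% of the recalled women by using CESM". CESM is barred in the control arm. The Discussion closes by expecting higher specificity at similar sensitivity. The article lists no comparison of cancers detected per randomised woman.

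**The concern.** Each woman receives one strategy, so no woman's disease status is judged by both. Randomisation balances the true number of cancers between arms, but not the number that becomes known. A cancer that only CESM can show enters both numerator and denominator of sensitivity in the CESM arm. Its counterpart in the control arm enters the denominator, as a false negative, only if it becomes an interval cancer or is found through the next screening round. If it stays silent, the woman is classed as a true negative.

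The control arm then looks better on sensitivity and NPV than it is. How much better depends on the share of occult cancers that surface within two years, and the article does not give this share. At stake is the conclusion on sensitivity. One and the same gain in detection could be reported as similar sensitivity or as a clear advantage for CESM.

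**Working it through.** **The plan's own figure.** For 40% versus 55%, two-sided 5% (sidedness is not stated) and 80% power:

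n = [1.96·√(2·0.475·0.525) + 0.8416·√(0.24 + 0.2475)]² / 0.15² = 173 per group.

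The Kelsey variant gives 174. The plan's 176 is close to both. Then 176/0.7 = 251 per group and 502/0.95 = 528, as stated. These figures concern specificity only.

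**Inputs from the article.** 251 evaluable women per arm; 30% malignancy, so 75 index cancers; up to 4% occult cancers, so 0.04 × 251 = 10.04 per arm.

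**Assumptions.**
- Sensitivity for index cancers is 94% in both arms. This is the value s that solves 0.877·0.7 / [0.877·0.7 + 0.3·(1 − s)] = 0.971, using the specificity of 87.7% and NPV of 97.1% that the Discussion quotes from a retrospective study. It gives s = 0.939. Applying this trial's 30% prevalence to that study is itself an assumption.
- Occult cancers occur in women without an index cancer. CESM finds all of them at work-up and conventional work-up finds none.
- A fraction f of the control arm's occult cancers surfaces within two years, each counted as a false negative. The article gives no value for f, so the whole range is shown.

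**Detected cancers.** Control: 0.94 × 75 = 70.5. CESM: 70.5 + 10.04 = 80.54. Per randomised woman: 70.5/251 = 28.1% and 80.54/251 = 32.1%. The difference is 4.0 points whatever f is.

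**Sensitivity.** CESM: 80.54/85.04 = 94.7%. Control: 70.5/(75 + 10.04f).

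| f | Cancers counted, control | Sensitivity, control | Difference (CESM 94.7%) |
|---|---|---|---|
| 0 | 75.0 | 94.0% | +0.7 |
| 0.25 | 77.5 | 91.0% | +3.8 |
| 0.5 | 80.0 | 88.1% | +6.6 |
| 1 | 85.0 | 82.9% | +11.8 |

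The last row is the true contrast in this scenario, since every cancer is then counted. Each smaller f understates it.

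**NPV and PPV**, with the planned specificities of 40% and 55%:
- Control NPV = 0.40·(251 − D) / [0.40·(251 − D) + 4.5 + 10.04f], where D = 75 + 10.04f. It is 94.0% at f = 0 and 82.0% at f = 1, against 95.3% for CESM.
- Control PPV = 70.5 / [70.5 + 0.60·(251 − D)]. It is 40.0% at f = 0 and 41.5% at f = 1, against 51.9% for CESM. It barely moves with f.

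**Other inputs.** Across 30–40% prevalence (the Background's six in ten without cancer implies about 40%), 3–4% occult cancers and 90–95% index sensitivity, the apparent sensitivity gain runs from 0.3 points (lowest, f = 0) to 11.8 points (highest, f = 1).

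**Precision of the per-woman comparison.** Half-width of the 95% CI: 1.96·√[(0.281·0.719 + 0.321·0.679)/251] = 8.0 points. Power for a 4-point difference: Φ[(0.040 − 1.96·√(2·0.301·0.699/251)) / 0.0409] = Φ(−0.98), about 16%.

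**The case against.** The plan does not count only what each work-up reveals. Both arms share two years of follow-up and the next screening round, and missed control-arm cancers that surface are counted as false negatives. This stands: the bias is confined to cancers that remain silent, and it vanishes if all surface.

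A reader might infer that the sensitivity comparison cannot show whether CESM finds more cancers. The table above does not support that: the contrast moves towards its true value as more cancers surface, and it nearly disappears only when almost none do. A reader might also extend the point to PPV. Predictive values are divided by test-positive or test-negative women, and denominators that differ by arm are inherent to them. NPV is affected through uncounted false negatives; PPV hardly is. Nor is it right that the article ignores the randomised women, since it plans intention-to-treat analyses; what is not listed is a per-woman detection measure.

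The size rests on assumptions that lean towards a large effect. Four percent is the top of the stated range. Control women may have tomosynthesis, ultrasound, MRI or follow-up imaging, which may reveal some of these cancers, and the article does not say whether occult means hidden on screening or on the full conventional work-up. Milder inputs shrink the range but leave the mechanism intact.

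Finally, the article expects similar sensitivity and does not set out to prove a higher detection rate, and the per-woman comparison has little power: 28.5% versus 32.5% would need about 2,079 women per arm for 80%. That limits what the added rate can establish. It does not remove the bias from the planned contrast.

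**Conclusion.** The point holds for sensitivity and NPV. Their comparison between arms is subject to differential verification, because cancers that only CESM reveals are certain to be counted in one arm and counted in the other only if they surface. The direction is known: against CESM. This mechanism can hide a gain, and nothing in it produces a false claim of superiority. A finding of similar sensitivity would therefore be hard to interpret.

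Under the stated assumptions, a fixed 4-point gain in detection per woman shows as anything from +0.7 to +11.8 points of sensitivity. The share surfacing and the assumption that conventional work-up finds no occult cancer are not supported by figures in the article, so this is a range and not an estimate of the bias. The point gives no ground for replacing specificity as the powered measure.

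**What to change.** In Statistical analysis, add beside sensitivity and NPV, for all randomised women by intention to treat:

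- cancers confirmed through the initial work-up per randomised woman, as a risk difference with 95% CI;
- interval plus next-round cancers per randomised woman, in the same form.

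Base any statement that CESM finds as many or more cancers on these rates, and state that the sensitivity and NPV contrasts are subject to differential verification. Specificity stays as the powered measure, and sensitivity, PPV and NPV can continue to be reported as planned.

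The cost is protocol or analysis-plan wording and a few derived variables; no new data are needed. The downside is precision: with an interval of about ±8 points and about 16% power for a 4-point difference, the detection rate must be presented as an estimate, and the claim on detection becomes more modest.
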